#### Which BB will be used

Propranolol is an ideal BB agent as shown in some observational studies because of its non-selective inhibition and lipophilic properties, and thus, it has a potential to reduce secondary injury and stress after TBI [25, 31]. Moreover, propranolol is a cheap BB agent available in a generic form only and has plasma half-life of 2 h after its intravenous administration. It is completely absorbed after oral use with peak plasma concentrations occurs 1–2 h in a fasting patient [32]. The liver eliminates around 90% of the oral dose with an elimination half-life of 3 to 6 h. It is widely and rapidly distributed throughout the body especially in the lungs, liver, kidney, brain, and heart [32].

#### Propranolol administration protocol

The current study will examine the early use of propranolol which will be administered for the initial 6 days post-injury. The first dose of propranolol will be administered within the first 24 h of hospital admission at 1 mg intravenous every 8 h for 2 days, followed by 1 mg propranolol intravenously every 12 h for another 2 days and finally 1 mg propranolol will be administered intravenously at every 24 h for 2 days (oral propranolol will be given to patients who are alert and can swallow). Heart rate and blood pressure will be recorded before giving the BB/placebo dose and throughout the study period.

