### Participants and study setting

The trial setting is the Hamad level I Trauma Centre in the state of Qatar, and the study subjects will be screened and enrolled from the trauma room in the emergency department (ED). Inclusion criteria are adult patients (≥ 18 to ≤ 65 years old) who sustained mild-to-severe blunt TBI (head AIS 1-5 and/or GCS 4-15), screened and enrolled within the first 24 h post-trauma.

Exclusion criteria are non-survivable injuries (head AIS = 6 and GCS = 3), uncontrolled bleeding on arrival to ED, SBP ≤ 100 mmHg (or MAP < 70 mmHg) not responding to initial resuscitation or required to be maintained on vasopressors for persistent hypotension (up to 24 h), patients with bradycardia [HR < 60] (re-assess every 2 h), pregnant women, prisoners, known to have severe bronchial asthma, and who requires emergency surgery < 6 h and no longer under trauma team care.

We expect to recruit a total of 771 TBI patients over 2 years. On hospital arrival, all TBI patients will have an initial head CT scan and managed according to the Advanced Trauma Life Support (ATLS) guidelines. We have a neurocritical care team with the state-of-art monitoring, imaging, and management of TBI. For this study, all mild-to-severe TBI patients who required hospital admission will be screened and enrolled by the attending physician and assigned nurse, if the subject meets the eligibility criteria. All enrolled patients will be tested for HsTnT (on admission and to be repeated after 6 h if the first reading is normal) and those who had positive HsTnT will receive BB, if no contraindication (group 1). Subjects with negative HsTnT (2 consecutive tests) will be randomized to either group 2, HsTnT –ve and BB use, or group 3, HsTnT –ve and no BB (placebo) (SPIRIT, Fig. 1).

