#### Randomization

The total number of HsTnT negative TBI patients will be randomized into two groups on the basis of administration of BB or no BB (placebo) with an allocation ratio of 1:1. The random number sequence will be generated using a random number table (simple randomization) which will be sequentially numbered and sealed in opaque envelopes of block size of ten.

The “randomization with concealment” procedure will be used for the allocation of patients into different randomization groups. The random number sequence will be generated using the Robust Randomization App (RRApp) which is a publicly available resource to generate rigorous and reproducible randomization schemes. We will generate the random number sequence by the process of simple randomization with a block size of ten which will be sequentially numbered and kept in sealed opaque envelopes for treatment assignment. Furthermore, to minimize the selection bias, we will strictly maintain allocation concealment from those assigning participants to study groups, implementation of protocolized treatment for all study participants, and blinded assessment of the primary outcome by trained research staff unaware of the sequence. Subjects will be enrolled in the trial by the study team, and the randomization for BB use among the HsTnT-negative group will be on double-blind basis. Details will be documented on the wristband and label (patient’s initials, date and time of randomization). The physician/nurse will document the randomization of the patient on the case report form. The wristband and label in the patient’s medical record will alert hospital staff to the patient’s enrolment in the trial.

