#### Blinding

Active and control study medications will appear identical. The treatment packs will be numbered, and the codes will be kept confidential and not broken until needed for emergency unblinding. The unique study ID number printed on the trial pack and the contents within the pack will be the only way to determine whether a pack contains active drug (propranolol) or placebo (0.9% normal saline).

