#### Study consent

There are 4 types of consent included in this study protocol. This study involves a time-critical intervention in TBI patients who may be unconscious, unable to consent to participation or no next of keen available within the therapeutic window of the study; therefore, a deferred consent will be obtained for subject’s enrollment in the study and signed by 2 physicians. In this case, the subject will receive the allocated study intervention provided by the treating independent physician and a study team member. Whenever available, the participant’s next-of-kin will be asked to sign consent to continue subject’s participation in the study. Patient who recovers enough cognition to understand the details of the consent will be asked to consent for continuation in the study (delayed informed consent). Patient, who presents with mild injury and can communicate well, will be asked to sign a written formed consent. In all the scenarios, a copy of the consent will be provided and refusal or withdrawal from the study at any time is the patient right and this will not affect his access for full standard of care management. The consent will allow the subject to permit/or decline the use of leftover blood samples to be used for further research.

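### For randomised patients who are alert, oral propranolol is provided for but the only placebo named is saline, so the route of dosing can reveal the arm

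*Protocol article*

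**What the plan says.** The section on propranolol administration gives the default route as intravenous, starting "at 1 mg intravenous every 8 h for 2 days" and stepping down in frequency over six days. It closes the regimen with a parenthesis: "oral propranolol will be given to patients who are alert and can swallow".

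The Blinding section promises that "Active and control study medications will appear identical". It says that the study ID and the pack's contents are the only means of telling "whether a pack contains active drug (propranolol) or placebo (0.9% normal saline)". That is the only place where the article says what the placebo is.

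The Randomization section limits the blinded comparison: "the randomization for BB use among the HsTnT-negative group will be on double-blind basis". Group 1 (HsTnT-positive) all receive propranolol unless contraindicated and lie outside it.

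Alert patients are plainly part of the population. Eligibility covers "mild-to-severe blunt TBI (head AIS 1-5 and/or GCS 4-15)", and the consent section has a separate path for the "Patient, who presents with mild injury and can communicate well".

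**The concern.** Saline can pass for an intravenous dose of propranolol, but it is not an obvious match for an oral one. If an alert patient in group 2 takes propranolol by mouth while an alert patient in group 3 can only be given saline, the route identifies the arm to the patient, the nurse and the physician without anyone opening a code.

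Staff who know the arm can manage it differently, through co-treatment, decisions on withholding a dose, and the timing of discharge. Patients who know it can disclose it when functional status is scored. The outcomes most exposed are length of stay, FIM and GOS, all listed as secondary endpoints. Double-blinding is in the trial's title, and the Discussion presents the lack of double-blind trials as the gap to be filled, so a route by which it can fail deserves correction.

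**Working it through.** No formula decides this point. The check is whether the stated rules can all be followed for the same patient.

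1. **Who is blinded.** Groups 2 and 3 only (Randomization section).
2. **Can a blinded patient be alert and able to swallow?** Yes. GCS up to 15 is eligible, mild injury is included, and some patients are expected to sign their own consent. Dosing runs for six days, so others may become alert during treatment.
3. **What would such a patient receive in group 2?** Under the parenthesis, propranolol by mouth. The next sentence of that section speaks of the dose of beta blocker or placebo, so the section is not written for the open group 1 alone.
4. **What would such a patient receive in group 3?** The article does not say. The only placebo named is saline. Its route is not stated; intravenous is inferred from its pairing with the intravenous drug.
5. **Do the rules fit together?** Not as printed. Under the Blinding section, the pack ID and contents "will be the only way to determine whether a pack contains active drug (propranolol) or placebo". An oral dose against a saline injection would be a second way. The commitment to identical appearance holds only if an oral control exists, and none is described.

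**How many patients.** The sample-size paragraph gives 257 per group and 771 in total (3 × 257 = 771). The two blinded groups together are 2 × 257 = 514. The article gives no proportion of alert patients and no count of oral doses, so the number exposed lies between 0 and 514. The introduction reports positive HsTnT in 65% of moderate-to-severe TBI at this centre and a likely dose-response between myocardial injury and head-injury severity. This suggests that the HsTnT-negative group leans towards milder injury, but it does not yield a share.

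**Which outcomes.**
- 10- and 30-day mortality: objective, with blinded assessment stated.
- Length of stay: depends on discharge decisions by treating staff.
- FIM and GOS: scored by people, GOS in clinic or by telephone. The article states blinded assessment for the primary outcome only.

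**Why leaving out orally dosed patients would not repair the analysis.** On the literal reading, oral doses occur only in the propranolol arm. Take assumed figures for illustration: half of each arm alert with 2% mortality, the other half with 20%, and no drug effect.
- All patients, each arm: 0.5 × 2% + 0.5 × 20% = 11%, so the difference is 0.
- Orally dosed patients removed: propranolol 20%, placebo still 11%.
- Apparent harm: 20% − 11% = 9 percentage points, created entirely by the exclusion.

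**The case against.** The strongest reply is that this is a condensed article. Pharmacy detail such as a matched oral form is often left to the full protocol, and the promise of identical appearance is not limited to the intravenous drug. The article also never says that an alert control patient stays on injections. This stands in part: it is not established that no oral placebo exists. It does not remove the conflict, because the article does more than stay silent. It names an oral form of the active drug and defines the placebo as saline. If an oral placebo exists, the definition in the Blinding section is incomplete as published.

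The scope of the parenthesis is also open. It follows the last, once-daily phase and might apply to that phase or to all six days. This limits what can be said about extent and is itself something to clarify.

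On consequences, the primary outcome is mortality, its assessment is stated to be blinded, and the analysis is to be blinded to assignment. These safeguards stand for the primary outcome. They do not restore the blinding of patients and treating staff, and they do not cover length of stay, FIM or GOS.

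A reader might also infer that revealed assignments, together with blocks of ten, make later allocations predictable. The documents do not support building on this. The Randomization section describes both simple randomisation and a block size of ten, with sealed opaque envelopes and concealment from those assigning patients, so the scheme in use is unclear.

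**Conclusion.** The conflict is real and confined to groups 2 and 3. As printed, the route of dosing can reveal the arm of an alert randomised patient. This rests on two inferences: that the saline is given intravenously, and that the article omits no oral placebo held elsewhere.

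A reader might infer that the double-blind design has failed, or that most randomised patients are unblinded. The documents support neither. They give no share of patients dosed orally, so the extent is unknown between none and all of the 514 planned. The mortality comparison is largely protected, apart from indirect effects through co-treatment and withheld doses. The direct risk is to length of stay, FIM and GOS. The point calls for correction but does not by itself undermine the primary result.

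**What to change.** - Reconcile the administration and Blinding sections. State how control patients in groups 2 and 3 are dosed whenever the active drug is given by mouth, and to which dosing days the oral provision applies.
- Provide an identical-looking placebo in the numbered pack for every route used for propranolol in these groups. Apply one route rule to both arms, decided without knowledge of assignment.
- Record the route of each dose on the case report form.
- Have FIM and GOS scored by existing staff who have no access to the drug chart.
- Recruitment began on 29 December 2020, so some patients may already have been dosed orally without a match. If so, report this and explore its effect by a baseline criterion applied equally to both arms, such as the admission GCS stratum already planned. Do not exclude patients because they were dosed orally.

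The cost is the pharmacy work of supplying and packing an oral placebo, plus an amendment; no extra patients or visits are needed. The change cannot restore blinding for doses already given. Which route or dose is right is a matter for the sponsor, and no position is taken here.

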#### Imaging and laboratory investigations

Once head injury is suspected, serum HsTnT test will be done, and patient will be sent to have a head CT scan. ECG will be done on admission and patient will have an echocardiography if troponin test comes positive and/or abnormal ECG (i.e., ST-T changes). S100B, enolase, epinephrine, cytokines (IL-1b,Il-6,Il-8,and Il-18), blood hemoglobin, platelet count, international normalized ratio, prothrombin time, activated partial thromboplastin time, blood glucose level, C- reactive protein, serum creatinine, urea, lactate, base deficit, sodium, and potassium. Epinephrine, brain, and inflammatory markers tests will run in duplicates. HsTnT was assayed using Elecsys (Roche Diagnostics International Ltd.). Myocardial injury will be defined as HsTnT cut-offs of 14 ng/L for women and 22 ng/L for men or a single cut-off of 19 ng/L [33].

#### Strategies to improve adherence to intervention protocols

Regular educational meetings, auditing, and agreement with the medical staff and neurosurgeon will be followed on regular basis to address the logistics for drug administration, precautions, and potential side effect and its management.

#### Randomization

The total number of HsTnT negative TBI patients will be randomized into two groups on the basis of administration of BB or no BB (placebo) with an allocation ratio of 1:1. The random number sequence will be generated using a random number table (simple randomization) which will be sequentially numbered and sealed in opaque envelopes of block size of ten.

The “randomization with concealment” procedure will be used for the allocation of patients into different randomization groups. The random number sequence will be generated using the Robust Randomization App (RRApp) which is a publicly available resource to generate rigorous and reproducible randomization schemes. We will generate the random number sequence by the process of simple randomization with a block size of ten which will be sequentially numbered and kept in sealed opaque envelopes for treatment assignment. Furthermore, to minimize the selection bias, we will strictly maintain allocation concealment from those assigning participants to study groups, implementation of protocolized treatment for all study participants, and blinded assessment of the primary outcome by trained research staff unaware of the sequence. Subjects will be enrolled in the trial by the study team, and the randomization for BB use among the HsTnT-negative group will be on double-blind basis. Details will be documented on the wristband and label (patient’s initials, date and time of randomization). The physician/nurse will document the randomization of the patient on the case report form. The wristband and label in the patient’s medical record will alert hospital staff to the patient’s enrolment in the trial.

#### Blinding

Active and control study medications will appear identical. The treatment packs will be numbered, and the codes will be kept confidential and not broken until needed for emergency unblinding. The unique study ID number printed on the trial pack and the contents within the pack will be the only way to determine whether a pack contains active drug (propranolol) or placebo (0.9% normal saline).

#### Emergency unblinding

In the unlikely event of an emergency where the appropriate treatment of the patient requires knowledge of the study drug, the site investigator may unblind the treatment assignment by contacting the research coordinator assigned for emergency unblinding. The study code should only be broken when the treating physician consider that the clinical treatment relies crucially on whether the patient received BB or placebo.

#### Withholding (temporary cessation of BB protocol)

As per the BB protocol, vital signs such as HR and SBP will be specifically monitored before administration of the next dose of propranolol. The study therapy (active or control) will be withheld, if the HR drops ≤ 70 beat/min, SBP ≤ 100 mmHg (with no response to fluid resuscitation within 2 h), or MAP < 70 mmHg. Patients initiated on the BB protocol and in whom there is failure to continue the subsequent doses of propranolol as per the BB protocol will also remain in the study and will be followed as per protocol. Data from such cases will also be analyzed based on the intention-to-treat principle.

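### A patient with a heart rate of 60–70 may be randomised, yet study therapy is withheld at 70 or below: the two limits conflict

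*Protocol article*

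**What the plan says.** **Entry.** The exclusion list under Participants and study setting names "patients with bradycardia [HR < 60] (re-assess every 2 h"). A rate of 60 or more is not excluded.

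**Withholding.** The section on temporary cessation of the protocol states: "The study therapy (active or control) will be withheld, if the HR drops ≤ 70 beat/min".

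**Blood pressure.** Entry excludes "SBP ≤ 100 mmHg (or MAP < 70 mmHg) not responding to initial resuscitation"; the withholding rule uses "SBP ≤ 100 mmHg (with no response to fluid resuscitation within 2 h), or MAP < 70 mmHg".

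**Checks before dosing.** The Propranolol administration protocol has: "Heart rate and blood pressure will be recorded before giving the BB/placebo dose and throughout the study period". The withholding section says that heart rate and SBP "will be specifically monitored before administration of the next dose of propranolol".

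**Analysis.** Patients who start the protocol and miss later doses remain in the study: "Data from such cases will also be analyzed based on the intention-to-treat principle".

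**Who is randomised.** Only HsTnT-negative patients, to "administration of BB or no BB (placebo) with an allocation ratio of 1:1". HsTnT-positive patients (group 1) receive propranolol without randomisation.

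**Sample size.** The Statistical analysis plan section gives 257 per group (771 in total), based on a 12% mortality reduction, 80% power, 5% alpha and 5% dropout. The Discussion gives the source rates as 36% without and 24% with beta blockers.

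**The concern.** The two heart-rate rules leave an interval, 60 to 70 inclusive, in which a patient is fit to be randomised but already at or below the level at which therapy is withheld. The article does not explain the gap. The two-hourly re-assessment of bradycardia appears to let in patients whose rate has risen only just to 60, still below the dosing limit.

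The statistical stake is dilution. Missed propranolol doses reduce exposure in the active arm, while missed placebo doses change nothing in the control arm. Under intention to treat, which is the right principle here, any resulting loss of effect shrinks the observed mortality difference. The planned effect comes from a retrospective comparison with patients who had received beta blockers, and the only stated inflation is for dropout. Group 1 also loses exposure if it follows the same rule, although it is not part of the randomised contrast.

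**Working it through.** **1. The limits side by side**

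| Measure | Entry exclusion | Withholding | Same value? |
|---|---|---|---|
| Heart rate | < 60 | ≤ 70 | No |
| SBP (mmHg) | ≤ 100 | ≤ 100 | Yes |
| MAP (mmHg) | < 70 | < 70 | Yes |

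For blood pressure only the numbers agree. At entry both limits are tied to non-response to resuscitation or to vasopressor need; in the withholding rule MAP carries no such condition.

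**2. How often the rule is checked.** Every 8 h for 2 days, every 12 h for 2 days and every 24 h for 2 days gives 3×2 + 2×2 + 1×2 = 12 scheduled intravenous doses. Each has a heart-rate reading beforehand.

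**3. Reproducing the planned sample size.** Inputs: p₁ = 0.36, p₂ = 0.24, two-sided 5% (sidedness is not stated), 80% power; p̄ = 0.30.

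n = [z₀.₉₇₅ √(2p̄(1−p̄)) + z₀.₈₀ √(p₁(1−p₁) + p₂(1−p₂))]² / (p₁−p₂)²

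= (1.960 × 0.6481 + 0.8416 × 0.6425)² / 0.0144 = 227.7, so 228.

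With continuity correction: (n/4)[1 + √(1 + 4/(n × 0.12))]² = 244.1, so 245.

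With 5% dropout: 245/0.95 = 257.9, so 258; or 244.1/0.95 = 256.9, so 257 if rounding is left to the end. The plan states 257. Without the correction the result is 240, and the one-sided versions give 190 and 207, so the two-sided, continuity-corrected calculation is the one that fits.

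**4. Worst-case illustration of dilution.** Let f be the share of the active arm affected. The article gives no value, so f is assumed. Give these patients the full control risk, that is, no benefit at all: p₂ = 0.24 + 0.12f, and the difference is 0.12(1−f). Evaluable patients per arm: 257 × 0.95 ≈ 244.

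Power = Φ{ [ (p₁−p₂) − 1/n − z₀.₉₇₅ √(2p̄(1−p̄)/n) ] / √[(p₁(1−p₁) + p₂(1−p₂))/n] }, with p̄ recalculated for each f. The 1/n term is the continuity correction.

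| f (assumed) | p₂ | Difference (points) | Power, corrected | Power, uncorrected |
|---|---|---|---|---|
| 0 | 0.240 | 12.0 | 80% | 83% |
| 5% | 0.246 | 11.4 | 75% | 78% |
| 10% | 0.252 | 10.8 | 70% | 74% |
| 20% | 0.264 | 9.6 | 59% | 63% |

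**The case against.** **The first dose may not be affected.** The withholding section is headed as temporary cessation. It speaks of a rate that falls, of the next dose, and of patients already started on the protocol. That reads most naturally as a rule for continuing treatment. A reader might infer that patients at 60–70 receive nothing; the article does not establish this. The reading taken before dosing makes it possible, but no threshold is attached to that reading. The objection stands as far as the first dose is concerned. It does not remove the conflict for later doses, and the ambiguity itself means that two members of staff could handle the same patient differently.

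**Withheld is not untreated.** The rule works dose by dose over about 12 doses, the first dose may come at any time in the first 24 h, and a rate of 60–70 at entry need not last. This stands, and it is why the power table is a worst case.

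**The base rates do not fit the randomised patients.** The 36% versus 24% comes from severe TBI, whereas the randomised patients are HsTnT-negative with mild-to-severe injury. The Introduction's own figures (26% mortality, 65% positive, fourfold mortality in positives) imply roughly 0.26/(0.65 × 4 + 0.35) = 9% mortality in HsTnT-negative patients, from which a 12-point fall is impossible. This also stands. It is a separate matter, but it means that the table shows the effect on the plan's own calculation and does not predict this trial's power.

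**Unequal withholding and hints of allocation.** A reader might blame the mismatch for more doses withheld on propranolol than on placebo, and for clues to allocation. Both could arise under any heart-rate withholding rule, because the drug lowers heart rate. Aligning the limits would cure neither, so they are not counted as harms of the mismatch.

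**Conclusion.** The conflict is real and nothing in the article resolves it: entry and withholding use different heart-rate limits, so a patient can be randomised while already at or below the level at which therapy is withheld. That such a patient stands to lose at least later doses, while the rate persists, follows directly from the text. That the patient receives no dose at all does not.

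The cost is reduced propranolol exposure within an intention-to-treat comparison whose sample size makes no stated allowance for it. Its size cannot be derived. The fall from 80% to about 75%, 70% or 59% rests on three things: an assumed share of 5%, 10% or 20%, zero benefit in every affected patient, and the plan's own 36% versus 24%. It shows that even a small affected share could matter to the planned calculation. It should not be read as an estimate of the power this trial will have.

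**What to change.** The sponsor should reconcile the heart-rate limit under Participants and study setting with the one in the withholding section, so that a patient cannot be randomised while already meeting the withholding rule. The amended text should also say whether that rule applies to the first dose. Which limits to use is a clinical decision for the sponsor, and none is proposed here.

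Keep all randomised patients in the intention-to-treat analysis, as planned. Add a summary of withheld doses by arm and by baseline heart rate; the vital signs needed are already recorded before dosing.

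The cost is a wording amendment and, depending on how the limits are reconciled, slightly fewer eligible patients.
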